#### Study 2: Evaluation of the feasibility and acceptability of passive dietary assessment devices in households in Ghana and Uganda

The purpose of this study is to evaluate the feasibility, acceptability, and performance of passive assessment devices in capturing food acquisition, preparation, and intake of households in Ghana and Uganda. In addition, this study aims to collect information on household structure, food, and eating behavior through an in-depth household interview, to inform the configuration and deployment of the camera devices appropriate for the food environment and eating culture of households in Ghana and Uganda.

Twenty-eight households (14 in each country) will be recruited and enrolled into the study. Prior to the recruitment of households, comprehensive community engagement meetings will be held with the community liaison office of the host institution, area government nutrition and health offices, community elders, and members of the communities to discuss the study and the use of camera devices to capture images of household food acquisition, preparation, and intake. Concerns raised by the communities will be addressed before the recruitment of households or start of the study.

Community elders and local field staff will help in identifying households for recruitment. Households will be enrolled when they meet these inclusion criteria: *1*) has ≥1 parent (mother or father); *2*) has a child or children aged <5 y and/or adolescent child/children (aged 10–19 y); *3*) members of the household eat the same prepared meal (i.e., each member does not prepare and eat separately); and *4*) willingness to use camera devices to record food preparation and intake. Enrollment of households will be through the household head or the primary food preparer, other adults in the households, and assent of teenagers.

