When an agreement on the deployment of the devices within the households has been reached, testing of the feasibility and acceptability of the devices will commence. This testing will occur within a week, including a weekend day, in the following order:

*Day 1 (household training on the use of the devices)*. On this day, field staff will train household members how to wear the camera devices on their body. Each household member will be assigned only 1 device. The primary food preparer or representative will be trained how to mount the Foodcam in the kitchen or cooking area. If the household uses shared plates to eat, the members will be trained how to mount the device in the dining area of the household. The demonstration will include training on how to switch the devices on and off, how to record using the devices, and how to download the images captured by the devices. During the training session, staff will address any questions or concerns that the participants have raised. After the training, a convenient day will be agreed with the household on the next day of testing the device. Depending on the size of the household, this training could take 1–2 h.

*Day 2 (first day of recording using the devices)*. On this day, Foodcam will be used to record all the food preparation/cooking in the household. Each member of the household will be given a camera device to record his/her food intake and food-related activities for the whole day. Local field staff will visit the households in the morning to supervise mounting of the Foodcam in the kitchen area and help household members with wearing their individual devices. The field staff will stay at the household for some time (between 30 min and 1 h) to ensure all the devices are properly mounted/worn and answer any questions or concerns answered. Field staff will take extra care to ensure their presence does not cause a great deal of inconvenience to household members and does not interfere greatly with their routine. Staff will conduct spot checks around the time of consumption of the household's main meals (i.e., breakfast, lunch, and dinner) to ensure all the devices are worn correctly. Finally, staff will return to the households in the evening, after the final household meal is eaten, to gather all the devices, thank the participants for their cooperation, arrange a convenient day for the next day of testing, and return to the project office.

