At the office, all the images will be downloaded, reviewed, and organized by meal. Any problems or challenges encountered during the recording will be discussed with the local study coordinator, site principal investigator, and the technology team to ensure the problems are rectified prior to the next day of testing the devices.

*Day 3 (assessment of battery life and user-friendliness of the devices)*. On this day, field staff will return to the household to test the battery life of the devices. This is important to establish whether the battery life in the field testing matches that of the manufacturer's expectation. The staff will also monitor the use of the devices by the participants. This involves assessing the ability of the participants to switch the devices on and off, recharge the devices using a portable charger, and connect to a laptop to download the images captured from the previous day of testing. This is to ensure families have full confidence in the devices and hopefully minimize any potential doubts about their use in the households. The staff will also address any problems encountered during data collection on the previous day and make sure household members are ready for using the device on the next day.

*Day 4 (second day of recording using the device)*. On this day, field staff will return to the household in the morning to provide a clean set of devices to use for that day and supervise their mounting and installation. The same procedure described above in Day 2 of testing will be followed. On this day, however, household members (except breastfed infants) will be assigned an individual wearable device different from the 1 they used previously, to ensure everyone has a feel of the different devices to help in the evaluation of the device's acceptability.

Finally, a field staff member different from those interacting with the households in the 4-d period will visit the households. S/he will present household members with a brief questionnaire to determine the acceptability of the devices among the study participants. The questionnaire will ask the household members to rate (from 1 to 5) the specific characteristic of each device such as ease of use, convenience on the body, how much it interferes with their eating and daily routine, how much they would like to use the device in the future, and their preferred choice of device. This questionnaire should take 10–15 min to complete.

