The following criteria will be used to assess the feasibility, performance, and reliability of the passive dietary assessment devices: 
Reliably records image/sensor data in the field with no or minimal missing data.Provides information to enable accurate identification of food, portion size estimation, and conversion to nutrients—i.e., sufficient image/data quality for a nutritionist to estimate nutritional intake.Usability—i.e., the device is user friendly and can be used by a nonengineer.Battery life—sufficient duration for the data collection session.Minimal recharge time—does not require any recharge during use or at most, only once.Comfortable and convenient to wear—no irritation to the wearer and does not disrupt their daily activities.Installation—easy to install/setup by household members in the field.Suitable for most households—i.e., device is rated at least average or above for acceptability (i.e., mean rating ≥3) from household members.

This phase of the study is crucial because it will inform whether the devices are of good acceptability and performance rating before proceeding to the validation study. In the event that the acceptability and performance of the devices are poor, we will work to improve the devices and/or the factors responsible for the poor performance to ensure the devices and conditions for testing are good enough to conduct a validation study.

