#### Study 3: Assessment of the validity of passive assessment method in estimating dietary intake in households in Ghana and Uganda

The purpose of this study is to test the validity of passive dietary assessment method relative to a weighed food record, in estimating an individual's dietary intake. The weighed food record is used as the gold standard method in this study. A tablet-based, interviewer-administered multiple-pass 24-h dietary recall will also be performed for comparison. Portion size picture aids will be used in the 24-h dietary recall.

Local field staff and community leaders will help in identifying 88 households (44 in each country) for enrollment in this study. The criteria for inclusion are the same as those described for Study 2. Foodcam will be mounted in the household's kitchen or cooking area to capture images of food preparation. Household members will be given a camera device to record their whole-day (waking hours) food intake, and the captured images will be used in the estimation of their dietary intake. However, only 2 randomly selected index cases (an adult and a child) in each household will have their corresponding dietary intake assessed using weighed food records and 24-h dietary recall. Dietary intake data from the devices and the 24-h dietary recall will be compared with weighed food records for accuracy evaluation. Prior to using the devices in the households, a questionnaire (similar to that used in Study 2) will be used to understand the structure, composition, and eating habits of the households to help implement a device deployment plan, especially for those who were not recruited in Study 2. To help recognize and effectively manage the data collection and logistical challenges that might arise in this study, this validation study will be conducted in 2 phases:

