*Phase 1: Pilot testing of the validation protocol in a sample population*. This phase is aimed at testing the study protocol in a sample of the households to help identify and address challenges that might arise during the data collection process. Study teams in the 2 countries will recruit 8 households each (16 households in total) for this purpose. The camera devices will be set up to record food preparation and intake in the households for a day. On the same day, the meals of the 2 index cases in each household will be weighed before and after eating. On the next day, a staff member not involved in the data collection on the previous day will visit the households to complete the multiple-pass 24-h dietary recalls—a method comprising multiple and sequential layers of questioning to increase accuracy in the reported food intake. The primary caregiver will complete the recall data for smaller children (especially those aged <5 y).

Data from the devices, weighed food record, and 24-h recall will be uploaded onto the cloud-based study database. These data will help determine the fidelity of the study protocol, robustness of the image capture and data transfer, identify challenges, and help inform any potential amendments to the protocol before the validation study in the target population.

*Phase 2: Validation in the target population*. In this phase, the passive dietary assessment devices will be validated in 88 households in the 2 countries. The devices will be set up to record food preparation and intake in the recruited households for 3 nonconsecutive days, preferably 2 weekdays and a weekend day. On each day, study staff will visit the households in the morning to mount the Foodcam in the kitchen/cooking area and help members of the household wear their devices. The devices will record an individual's food intake for the whole day during waking hours. At the end of each day, staff will return to the households to collect all the devices. In addition, the same staff will weigh and record the food intakes, before and after eating, of the index cases for the weighed food record measurement. After each day, a different staff member will visit the households to complete the 24-h dietary recall for the index cases.

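### Study 2 judges missing data, image quality and household installation only under staff-assisted device wear, so its results do not show unsupervised performance

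*Protocol article*

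**What the plan says.** **Study 2.** Two recording days are described, Day 2 and Day 4. On the morning of Day 2 staff supervise the mounting of Foodcam, help with the wearable devices, and stay for a while ("between 30 min and 1 h) to ensure all the devices are properly mounted/worn"). Later they make spot checks at about the times of the main meals: "i.e., breakfast, lunch, and dinner) to ensure all the devices are worn correctly". Day 4 repeats this: "The same procedure described above in Day 2 of testing will be followed". Day 3 tests battery life and whether participants can switch on and off, recharge and download. It is not a recording day.

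The list of criteria that closes Study 2 opens with "Reliably records image/sensor data in the field with no or minimal missing data". It also asks for image quality good enough for a nutritionist to estimate intake, and for easy installation by household members. The results are to inform readiness for the validation study. If they are poor, the devices or conditions are to be improved.

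**Study 3, Phase 2.** Staff mount Foodcam and help with wear in the morning. In addition, "the same staff will weigh and record the food intakes, before and after eating, of the index cases". The weighed reference is confined to index cases: "only 2 randomly selected index cases (an adult and a child) in each household will have their corresponding dietary intake assessed using weighed food records". No spot check of device wear is described for Study 3.

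**The concern.** Wearing the device properly, switched on and pointing the right way, is the main task that a passive method still leaves to the user. In Study 2 staff act on that task on every recording day, around the meals at which capture matters most. A device found off, removed or tilted is put right, and what it then records counts towards completeness and image quality. The same holds for installation, which is meant to be easy for household members but is observed while staff supervise the mounting.

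Two uses of the results are at stake. One is the decision that the devices are ready, or need improving: staff can improve only the failures they can see. The other is any later statement about reliability in households without field staff at mealtimes, for which Study 2 as described gives no direct evidence.

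**Working it through.** The article states no figure for this point, so there is none to reproduce. The check is a count of exposed days, a comparison of texts, and one line of algebra.

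**1. How much recording is free of checks?**
- Households: "Twenty-eight households (14 in each country) will be recruited and enrolled into the study", so 28.
- Recording days per household: 2 (Days 2 and 4).
- Household-days: 28 × 2 = 56.
- Days with scheduled checks: 56, since Day 4 follows Day 2. Days without: 56 − 56 = 0.
- With the three named meals a day, at most 56 × 3 = 168 household meals fall within the check schedule. This counts the schedule. It does not show that each check took place or came before eating.

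**2. Criteria against staff action.**
- *Missing data:* staff fit the devices in the morning and check wear around main meals. Loss from poor wear is affected. Loss from hardware, battery or storage is not.
- *Image quality:* alignment is affected by the same checks.
- *Installation by household members:* mounting is supervised on both recording days. Day 3 tests handling of the devices, but not wear while eating.

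**3. What the data can separate.** Let *p* be the share of meals with a wear failure before any check, *f* the share of these that staff put right in time, and *m* the wear-related loss observed. In the simplest case, where an uncorrected failure loses the meal:

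*m* = *p* × (1 − *f*), so *p* = *m* / (1 − *f*).

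The images give *m* only. To show the range, assume an observed loss of 4%:
- *f* = 0: *p* = 4%
- *f* = 0.5: *p* = 4% / 0.5 = 8%
- *f* = 0.8: *p* = 4% / 0.2 = 20%

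None of these values comes from the article. They show only that one observed completeness figure fits very different unassisted rates, and that the state as found is what would tell them apart.

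**4. Study 3.** Index cases: 88 × 2 = 176. Over 3 days this is 176 × 3 = 528 person-days on which food is weighed before and after eating, so staff are near the index meals. The text supports presence and morning fitting. It does not state that devices are checked or adjusted at meals.

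**The case against.** Much of the opposing case stands.

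- *The checks are spot checks.* They take place around main meals, are not continuous supervision, and leave snacks and eating away from home uncovered. This limits the effect but does not remove it, since the criteria are still never observed without the checks.
- *Study 2 is a readiness check for a study that also fits devices with staff help.* This is fair, and the criteria carry no numeric limit that could be passed too easily. But Study 3 describes no mealtime wear checks, so Study 2 was observed under more stated help than Study 3 provides.
- *A log of corrections may exist in the full protocol.* It may, and its absence from an article is no fault. The point concerns the state on which the criteria are judged. Problems met during recording are reviewed after the recording day, but that is not a wear rate.

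A reader might also infer four stronger things, which the article does not support:

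- *That the method is not passive.* The Introduction defines passive by minimal or no user input, not by the absence of field staff.
- *That Study 3 accuracy is inflated by correction at meals.* Correction there is not stated. Presence follows from choosing a supervised weighed record as the reference.
- *That the effect can be sized against the ±10% accuracy rule.* That rule, in the Analytical plan, concerns agreement with weighed records. Study 2 has none, and no wear-failure or correction rate is given.
- *That index and non-index members could be compared to measure an observer effect.* Non-index members have no weighed record or recall, so eating occasions the camera missed cannot be counted. Household members also share prepared meals, possibly with the same staff nearby.

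**Conclusion.** The point holds as a limit on what Study 2 can show. On all 56 planned household-days, missing data, image quality and household installation are assessed under staff-assisted wear, and unsupervised performance is not observed. The direction is towards more favourable figures, provided that staff correct at least some of the faults they find. The size is unknown. The article contains no contradiction or wrong figure here, and the checks themselves are reasonable in a feasibility study. What should change is how their effect is recorded and reported. For Study 3 the conclusion is narrower: accuracy will apply to staff-fitted wear with an observer present, and this should be said.

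**What to change.** **Study 2**
- At each spot check, record the state of every device as found (on or off, worn, aligned) before any correction.
- Report wear and capture completeness twice: as found, with a device found off, unworn or misaligned counted as a wear failure, and after correction.
- Use the as-found figure when judging the missing-data and installation criteria.
- Image quality cannot be scored on the uncorrected state for a meal recorded after correction. Report it as obtained under staff-assisted wear.

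**Study 3**
- Instruct weighing staff not to adjust or prompt devices after the morning fitting, and log any exception.
- State in the report that accuracy applies to staff-fitted wear with an observer present.

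**Cost:** a tick-box on the spot-check form, one instruction and a short log. The small downside is that the reliability figures will look less favourable.

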#### Study 3: Assessment of the validity of passive assessment method in estimating dietary intake in households in Ghana and Uganda

The purpose of this study is to test the validity of passive dietary assessment method relative to a weighed food record, in estimating an individual's dietary intake. The weighed food record is used as the gold standard method in this study. A tablet-based, interviewer-administered multiple-pass 24-h dietary recall will also be performed for comparison. Portion size picture aids will be used in the 24-h dietary recall.

Local field staff and community leaders will help in identifying 88 households (44 in each country) for enrollment in this study. The criteria for inclusion are the same as those described for Study 2. Foodcam will be mounted in the household's kitchen or cooking area to capture images of food preparation. Household members will be given a camera device to record their whole-day (waking hours) food intake, and the captured images will be used in the estimation of their dietary intake. However, only 2 randomly selected index cases (an adult and a child) in each household will have their corresponding dietary intake assessed using weighed food records and 24-h dietary recall. Dietary intake data from the devices and the 24-h dietary recall will be compared with weighed food records for accuracy evaluation. Prior to using the devices in the households, a questionnaire (similar to that used in Study 2) will be used to understand the structure, composition, and eating habits of the households to help implement a device deployment plan, especially for those who were not recruited in Study 2. To help recognize and effectively manage the data collection and logistical challenges that might arise in this study, this validation study will be conducted in 2 phases:

*Phase 1: Pilot testing of the validation protocol in a sample population*. This phase is aimed at testing the study protocol in a sample of the households to help identify and address challenges that might arise during the data collection process. Study teams in the 2 countries will recruit 8 households each (16 households in total) for this purpose. The camera devices will be set up to record food preparation and intake in the households for a day. On the same day, the meals of the 2 index cases in each household will be weighed before and after eating. On the next day, a staff member not involved in the data collection on the previous day will visit the households to complete the multiple-pass 24-h dietary recalls—a method comprising multiple and sequential layers of questioning to increase accuracy in the reported food intake. The primary caregiver will complete the recall data for smaller children (especially those aged <5 y).

Data from the devices, weighed food record, and 24-h recall will be uploaded onto the cloud-based study database. These data will help determine the fidelity of the study protocol, robustness of the image capture and data transfer, identify challenges, and help inform any potential amendments to the protocol before the validation study in the target population.

*Phase 2: Validation in the target population*. In this phase, the passive dietary assessment devices will be validated in 88 households in the 2 countries. The devices will be set up to record food preparation and intake in the recruited households for 3 nonconsecutive days, preferably 2 weekdays and a weekend day. On each day, study staff will visit the households in the morning to mount the Foodcam in the kitchen/cooking area and help members of the household wear their devices. The devices will record an individual's food intake for the whole day during waking hours. At the end of each day, staff will return to the households to collect all the devices. In addition, the same staff will weigh and record the food intakes, before and after eating, of the index cases for the weighed food record measurement. After each day, a different staff member will visit the households to complete the 24-h dietary recall for the index cases.

The dietary data collected from the households will be taken to the project office, where the images will be downloaded, reviewed, organized by meal, and uploaded onto the study database. Custom software (described below) will be used to identify the foods on the images, and estimate the portion size eaten and its nutritional content. Weighed food record and 24HR data will be analyzed by independent staff using nutritional analysis software (Dietplan) to estimate the nutritional content. The dietary intake from the images and 24HR will be compared with the weighed food record for accuracy evaluation.

The ethics committees (Institutional Review Boards) of University of Georgia, USA, and Noguchi Memorial Institute for Medical Research, Ghana, have approved Studies 2 and 3 for Ghana (approval reference: STUDY00006121 and IRB00001276, respectively). Studies 2 and 3 in Uganda have been approved by Mbale Regional Referral Hospital Research Ethics Committee (MRRH-REC) and the Uganda National Council for Science and Technology (UNCST) (approval reference: MRRH-REC OUT0051/2019 and HS2680, respectively).

